## Abstract

**Background:**

The MASS IV-DM Trial is a large project from a single institution, the Heart Institute (InCor), University of São Paulo Medical School, Brazil to study ventricular function and coronary arteries in patients with type 2 diabetes mellitus.

**Methods/Design:**

The study will enroll 600 patients with type 2 diabetes who have angiographically normal ventricular function and coronary arteries. The goal of the MASS IV-DM Trial is to achieve a long-term evaluation of the development of coronary atherosclerosis by using angiograms and coronary-artery calcium scan by electron-beam computed tomography at baseline and after 5 years of follow-up. In addition, the incidence of major cardiovascular events, the dysfunction of various organs involved in this disease, particularly microalbuminuria and renal function, will be analyzed through clinical evaluation. In addition, an effort will be made to investigate in depth the presence of major cardiovascular risk factors, especially the biochemical profile, metabolic syndrome inflammatory activity, oxidative stress, endothelial function, prothrombotic factors, and profibrinolytic and platelet activity. An evaluation will be made of the polymorphism as a determinant of disease and its possible role in the genesis of micro- and macrovascular damage.

**Discussion:**

The MASS IV-DM trial is designed to include diabetic patients with clinically suspected myocardial ischemia in whom conventional angiography shows angiographically normal coronary arteries. The result of extensive investigation including angiographic follow-up by several methods, vascular reactivity, pro-thrombotic mechanisms, genetic and biochemical studies may facilitate the understanding of so-called micro- and macrovascular disease of DM.

## Background

Diabetes mellitus is a potentially serious disease and is currently the major concern of public health officials. This disease has a prevalence of 2% to 5% in most Western countries and has grown exponentially around the world, possibly because of changing dietary habits in recent years [1-3].

Patients with type 2 diabetes often have cardiovascular risk factors that may further influence the prognosis of the disease. These risk factors compose metabolic syndrome. They include high blood pressure [4,5], dyslipidemia, and obesity, which have been reported as participating in the pathogenesis of cardiovascular events by possible action on coronary endothelial function [5]. Moreover, the high rate of urinary albumin excretion has been hypothesized as an additional indicator of endothelial dysfunction, which is associated with a higher rate of renal and cardiovascular events [6]. Other risk factors include potential age and sex [7], smoking [8], glycemic control, lipids [5,9], and hormone replacement therapies [10].

Major studies have shown that healthy endothelium inhibits adhesion of platelets and leukocytes to the vessel surface and maintains the balance of profibrinolytic and prothrombotic activity [11]. However, with the occurrence of dysfunction, the endothelium is a potential contributor to the pathogenesis of vascular disease in diabetes mellitus and atherosclerosis [12].

Under physiological conditions, there is a delicate and balanced release of relaxing factors and endothelium-derived contraction factors that apparently is imbalanced in diabetes and may contribute to the development of atherosclerosis, thus contributing to the further progression of vascular injury in different organs [13].

Hyperglycemia has been implicated as the main causal factor in the development of coronary atherosclerosis in diabetic patients. However, the mechanisms associated with this disorder are likely to be multifactorial. Among these are hypertension, abdominal obesity, and pluri-metabolic syndrome [14-16].

Besides these, we highlight the presence of decreased high-density lipoprotein and elevated low-density lipoprotein (LDL) cholesterol, high triglycerides, increased VLDL, nephropathy, altered coagulation, and platelet dysfunction. Insulin resistance, another existing condition in diabetes, has been described as responsible for the increased risk of death from coronary artery disease (CAD) [15-17].

The objectives of the MASS IV-DM Trial is to compare the clinical data, laboratory profile, and angiographic evolution at baseline with that at 5-year follow-up in patients with type 2 diabetes who have angiographically normal coronary arteries.

## Methods/Design

The MASS IV-DM Trial is an institutional project to be conducted at the Heart Institute (InCor), Hospital das Clinicas, University of São Paulo, and is designed to prospectively investigate 600 type 2 diabetic patients with a clinical suspicion of coronary insufficiency and electrocardiographic evidence of myocardial ischemia who have normal coronary angiographies and ventricular function.

It is designed as a secondary prospective cohort study. Only patients with angiographically normal coronary arteries (by semi quantitative TCA equal to zero) will be included in the study. After inclusion, all patients will undergo a 320-row multidetector computed tomography (MDCT) angiography of the coronary arteries to assess the calcium score as well as the plaque characteristics if present any. Both angiography studies will be repeated after 5 years of follow-up. Ischemia induced by stress electrocardiography and associated with myocardial nuclear scintigraphy will be performed at the beginning and end of the study. Furthermore, ventricular function will be measured by echocardiography at baseline, and vascular reactivity and endothelial function will be recorded at the beginning and end of the study. Laboratory tests will include a biochemical profile of blood lipids, renal function, urinalysis, genetic polymorphism, oxidative stress, and inflammatory activity, among others. All patients will undergo an outpatient clinical evaluation every 6 months. The schedule of activities is shown in Table 1.

**Table 1 T1:** Schedule of measurements.

	S	6	12	18	24	30	36	42	48	54	60
		m	m	m	m	m	m	m	m	m	m
History/events	X	X	X	X	X	X	X	X	X	X	X
Physical examination	X		X		X		X		X		X
Symptom assessment	X	X	X	X	X	X	X	X	X	X	X
Routine laboratory	X	X	X		X		X		X		X
Electrocardiography	X	X	X		X		X		X		X
Echocardiography	X		X		X		X		X		X
Stress MPI	X						X				X
Medications	X	X	X	X	X	X	X	X	X	X	X
Angiograms	X										X
CAC-Scan	X										X
Arterial stiffness	X										X
Resources utilization											X
Quality of life	X										X
Work status	X										X
Serious adverse events			Continuous								X

Abbreviations: S = baseline; 6m = 6 month after study entry; 12 m to 60 m denotes months after study entry. Stress MPI=Stress myocardial perfusion imaging, CAC-Scan=Coronary-artery calcium (CAC) scan

The MASS IV-DM Trial has an independent external committee that is blind to the clinical evaluation and will monitor the research. This external committee will analyze all clinical events including myocardial infarction, cerebrovascular events, and others. The role of this committee will be to ensure that clinical events will be assessed uniformly.

### Patients

Diabetic patients with clinically suspected (based on presence of the CCS II/III angina) or documented myocardial ischemia based on ET will undergo coronary angiography that will be performed according to the technique of Sones or Seldinger. For the evaluation of ventricular function, patients will receive contrast in the left ventricle, and measures will be taken with the patient in the right anterior oblique position. The calculation of left ventricular ejection fraction will be made according to the Dodge formula.

For the angiographic study of the coronary arteries, 5 views of the left coronary artery and 2 of the right coronary artery will be obtained. These effects allow a clear assessment of each coronary artery, thus forming 4 pairs of perpendicular incidence suitable for biplane analysis.

Nitrates or other vasoactive drugs will be available when needed. The same sequence of arteriographic projections, field X-ray, and size of catheters will be followed in each patient and similarly in subsequent examinations. These conditions will be crucial for the accurate assessment of the artery after 5 years of follow-up.

Possible changes in the lumen of the coronary arteries will be assessed visually and quantitatively. Two experienced observers are blinded to the identity of the patient during both tests and also for the sequence of films at the beginning and end of the study.

The pair of films, the initial and final will be seen both side by side with 5 times magnification in a projector system adapted for this analysis.

To evaluate the second angiogram, 2 incidences will be selected of a good quality at the same point in the cardiac cycle as on the first angiogram of each coronary artery studied. Based on direct visual comparison of the coronary arteries, by consensus, the arteries will be rated as unchanged, definitely changed, or possibly changed. For possibly changed, a third frame will be selected for each view from each film.

### Coronary artery calcium scan

It is assumed that the presence of calcium in the wall of the coronary arteries is a strong indicator for the diagnosis of coronary artery disease [30,31]. Previous studies using electron-beam computed tomography (EBCT) have suggested that EBCT has great potential for noninvasive quantification of calcium in the coronary arteries [32,33]. Furthermore, CAD is also related to the presence of calcium with luminal narrowing of coronary arteries and correlates with clinical, angiographic, and pathology data [34,35].

However, this method of investigation was unable to precisely define the percentage of luminal narrowing based only on the presence of calcium in the wall of artery.

Recent studies have focused attention on the uncertainties of visual estimates of the percentage of luminal narrowing compared with angiography, the difficulty of making visual estimates, and therefore their reproducibility [36,37], their predictive value, changes in the flow, and also in flow reserve [38,39].

Thus, to prevent this methodological bias, we plan to evaluate the presence of calcium in the arterial wall by performing a coronary artery calcium scan using EBCT at baseline and after 5 years of follow-up and to correlate these findings with angiographic data at the beginning and end of the study. This procedure can identify possible luminal narrowing and also eliminate any methodological flaw, because it compares similar examinations at the beginning and end of the study.

### Myocardial scintigraphy

To evaluate the presence of myocardial ischemia, even in the absence of coronary epicardial vessels, all patients will undergo myocardial scintigraphy during exercise at baseline and at the end of the study. The images of myocardial scintigraphy will be acquired through the tomographic technique (SPECT - Single Photon Emission Computed Tomography), synchronized with an electrocardiographic signal (*gated*), which allows for the simultaneous assessment of myocardial perfusion and a quantitative parameter of ventricular function, by using the 99mTc-Sestamibi (2-methoxy-isobutyl-isonitrile marked with technetium-99 m) as a myocardial perfusion marker.

With the patient under resting conditions, 740 MBq of 99 mTc-Sestamibi will be endovenously administrated to the patient, and the acquisition of images will be performed 60 to 90 minutes after the injection. Near the end of the stress test, 740 MBq of 99 mTc-Sestamibi will be introduced, and the patient will be stimulated to continue exercising for at least 1 minute, if possible. After the recovery stage, data will be recorded, and the patient will be placed under the gamma-chamber detector so that images can be obtained.

The acquisition of images will be performed in a noncircular orbit, starting from a RAO 45° projection to LPO 45° projection, thus completing 180° scan for tomographic images, at 64 frames in a 64 × 64 matrix (1 detection every 2.8° with a duration of 30s), using an energy of 140 keV windows. No coefficient of spreading attenuation or correction will be used. The images will be prefiltered with a 2-dimensional Butterworth filter with order 5, cutoff frequency of 0.6 Nyquist, and reconstructed through the iterative method (5 iterations) in a Sun computer, Ultra 60 model, through the AUTO SPECT + Instill 5.0 software, according to the existing recommendations [40,41]. The analysis of ejection fraction will be performed using AUTO QUANT 4.21 software. For the quantification of ischemic myocardium, a semi-quantitative assessment will be performed of a 17-segment model (short axis and long vertical axis will be separated into 6 segments in the apical, middle, and basal sections of the short axis, and in 2 apical segments in the long vertical section), retrospectively analyzed by at least 3 experienced observers, without any knowledge of clinical, ergometric, and cinecoronariographic data [41].

At the beginning of the study and at the end of follow-up, perfusion images will be analyzed and quantified through the 5-point semi-quantitative scoring system: 0 (normal), 1 (discreet reduction in captation), 2 (moderate reduction in captation), 3 (significant reduction in captation of radioisotopes), 4 (apparent absence of detectable captation at the follow-up).

The exercise score summed (ESS) index will be acquired by summing the scores of 17 follow-ups of exercise stress test imaging [42]. The resting score summed (RSS) index will be obtained in the same way, by summing the scores of 17 follow-ups of the image of captation at each examination of rest. To estimate the reversibility of the defect, the difference in the score summed (DSS) index will be calculated through the subtraction of the ESS from the RSS index.

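### Two scintigraphy scoring rules are wrong as written: the reversibility index (DSS) falls as reversible ischaemia worsens, and the described layout adds to 20 segments where 17 are named and summed

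*Protocol article*

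**What the plan says.** All of this stands in the Myocardial scintigraphy section of the protocol article.

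- **Layout.** The section announces that "a semi-quantitative assessment will be performed of a 17-segment model". The bracket that follows says the short and long vertical axes "will be separated into 6 segments in the apical, middle, and basal sections of the short axis, and in 2 apical segments" of the long vertical section.
- **Score per segment.** The scale is a "5-point semi-quantitative scoring system: 0 (normal), 1 (discreet reduction in captation"), rising to "4 (apparent absence of detectable captation at the follow-up"). Higher therefore means less uptake.
- **Sums.** ESS is obtained by "summing the scores of 17 follow-ups of exercise stress test imaging". RSS is obtained in the same way from the rest images, again over 17.
- **Difference.** To estimate how reversible a defect is, "the difference in the score summed (DSS) index will be calculated through the subtraction of the ESS from the RSS index".

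The section places the scans at baseline and at the end of the study; Table 1 also lists stress perfusion imaging at month 36. At least three observers read the images.

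**The concern.** The index meant to estimate reversibility appears to run opposite to its purpose. On a scale where a higher score is worse, a defect that appears on exercise and recovers at rest makes ESS exceed RSS, so RSS - ESS is negative, and more negative the more reversible the defect. A patient who develops ischaemia over the 5 years would show a falling DSS. Someone who took a higher DSS to mean more ischaemia would draw the opposite conclusion, and any cut-off applied in that direction would select the wrong patients.

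The segment layout does not produce the number of scores that the sums use. A reader following the bracket and a reader following the name of the model would fill in different forms. The images are read by several observers and compared about five years apart, so the layout has to be unambiguous.

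**Working it through.** **Inputs**, all from the Myocardial scintigraphy section: per-segment score 0 to 4, higher meaning less uptake; 17 scores in each of ESS and RSS; short axis "6 segments in the apical, middle, and basal sections of the short axis"; long axis "and in 2 apical segments in the long vertical section"; DSS formed by subtracting ESS from RSS.

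**1. Segment count.** The plan's figure is 17.

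- Six in each of three short-axis sections plus two apical: 6 + 6 + 6 + 2 = 20.
- The only other reading, six short-axis segments in total plus two: 6 + 2 = 8.

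Neither gives 17. On the natural reading the layout has 20 - 17 = 3 segments more than the sum.

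**2. Range of the sums.** The maximum is 4 times the number of segments.

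| Segments | ESS and RSS | DSS |
|---|---|---|
| 17 (named and summed) | 0 to 68 | -68 to +68 |
| 20 (layout described) | 0 to 80 | -80 to +80 |

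The ratio of the maxima is 80/68 = 1.18. A sum of 4 is 4/68 = 5.9% of the maximum on one scale and 4/80 = 5.0% on the other.

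**3. Direction of DSS.** Subtracting A from B is B - A, so the text gives DSS = RSS - ESS.

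| Illustrative case | ESS | RSS | As written, RSS - ESS | ESS - RSS |
|---|---|---|---|---|
| Fixed defect | 9 | 9 | 0 | 0 |
| Three segments at 2 on exercise, 0 at rest | 6 | 0 | -6 | +6 |
| Larger, mostly reversible defect | 10 | 3 | -7 | +7 |

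A patient who moves from ESS 3, RSS 3 at baseline to ESS 10, RSS 3 at 5 years has DSS going from 0 to -7 as written. New ischaemia is recorded as a decrease of 7.

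**4. What the sign does to inference.** RSS - ESS is exactly -1 times ESS - RSS. Every difference, correlation or slope that involves DSS keeps its size and changes its sign, and two-sided p values are identical. A check on simulated scores for 600 patients (Poisson counts chosen only for illustration, not trial data) agrees: the paired t statistic for change in DSS is 4.01 or -4.01 with the same p value, and the Spearman correlation with an artificial covariate is 0.71 or -0.71 with the same p value.

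**The case against.** The strongest reply is that these are translation slips with little consequence. Much of it stands.

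- **Reach of the sign error.** A reader might infer that the ischaemia scores as a whole are reversed. They are not: ESS and RSS run in the intended direction, and only DSS is affected.
- **Effect on the analyses.** A reader might infer that every correlation and regression coefficient for ischaemia will come out reversed. The Statistical analyses section names no correlation or regression on DSS. Its Spearman test and backward regression concern endothelium-dependent coronary vasoreactivity. The article also states no cut-off and no one-sided test for DSS.
- **Scale.** A reader might call the scale undefined. It is contradictory rather than undefined: 17 is stated three times, once as the name of the model and once in each of the two sums. Only the bracket points to 20.
- **Lost or mixed segments.** A reader might infer that three of 20 segments will be scored and then dropped, or that readers will mix two layouts. The article plans neither. These are things the contradiction permits, not things it prescribes. The 1.18 ratio compares theoretical maxima and is not an effect on any patient.
- **Weight in the study.** The article's stated goal rests on angiograms and the calcium scan. Scintigraphy is one of several other assessments.
- **Wording.** Summing over follow-ups, and defining score 4 at the follow-up, almost certainly means segments. The order of ESS and RSS may be the same kind of slip, although the text cannot show that.

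The reply does not make the text correct. The article chose to print a formula, a layout and a number of scores. The formula opposes its stated purpose, and the layout and the number cannot both be right. This is stated content, not detail that an article leaves to a fuller document.

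**Conclusion.** The point holds as two errors of definition, of minor to moderate severity.

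First, DSS as written has the opposite sign to the reversibility it is meant to estimate. Interpretation and any threshold invert; magnitudes, two-sided p values, ESS and RSS do not change. Second, the layout gives 20 segments (range 0 to 80) against 17 named and summed (range 0 to 68).

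This rests on three readings: subtraction in its ordinary English order; six segments in each short-axis section (the alternative total of 8 does not give 17 either); and follow-ups standing for segments in the summing rules. It also takes a reversible defect to be one that scores worse on exercise than at rest. The article does not show which layout the readers actually use, so no bias in results can be claimed.

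**What to change.** 1. State DSS = ESS - RSS, with a positive value meaning a reversible defect.
2. Make the segment layout add to the number of scores summed, either by correcting the bracket so that it adds to 17 or by naming and summing 20 segments. Print the resulting range (0 to 68 or 0 to 80).
3. Use that one layout for all readers and at every scan that is compared.
4. Replace follow-ups with segments in the two summing rules, and remove the reference to follow-up from the definition of score 4.

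**Cost.** A correction to the text and the reading form. DSS values already computed as written need only a change of sign. Scans read on 17 segments need nothing further. Scans actually read on a 20-segment layout cannot simply be re-summed to 17: they would need a mapping between layouts or a re-read, or else the sums must be restated as 20-segment sums throughout.

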### Doppler echocardiography

Changes in myocardial contractility in both systole and diastole are identified by Doppler-echocardiography. Thus, to assess the presence of variation in myocardial thickness or systolic-diastolic movements even in the absence of coronary epicardial vessels, all patients will undergo echocardiography at baseline and at the end of the study.

Patients will undergo examination with commercially available 2-dimensional echocardiographic ATL equipment, with an electronic transducer of 2.5 mHz. Intermediate examinations during follow-up will not be considered. For study purposes, echocardiographic patients will be free of medications at the beginning and end of the study. Normal LV systolic function will be considered > 50%.

For the echocardiographic examination, patients will be examined while in the left lateral position with a slight rotation of the thorax, and standardized apical and parasternal approaches. Echocardiographic records follow the recommendations of the American Society of Echocardiography.

The relaxation time of the left ventricle (TRIVE) will be determined by the simultaneous recording of intracavitary blood flow on Doppler measured at the end of the closure of the aortic and mitral valve opening, corresponding to the beginning of the E-wave.

The E-wave deceleration time is calculated by the time interval between the peak E-wave and the intersection of this line with that at baseline.

The tests will be analyzed by 3 observers. The first observer will assess the measures twice and a second observer once. The third observer will be available to resolve doubts. Interobserver and intraobserver variability will be identified and corrected by consensus.

### Arterial stiffness

All patients will be evaluated for vascular stiffness at baseline and at the end of follow-up. Measurement of arterial stiffness is considered to be particularly interesting in the proposed scenario since the absence of atherosclerotic obstructions indicated by conventional angiograms, and confirmed by coronary artery calcium scan, empowers in significance prospective changes in arterial mechanical properties. It is thus conceivable that this will be a useful tool in informing the development and possible progression of atherosclerotic disease. Arterial stiffness can be assessed noninvasively by different methodologies. The measurement of aortic pulse wave velocity is generally accepted as a very reliable method since it is simple, noninvasive, and reproducible, and can be compared periodically being supported by the greatest number of epidemiological studies for its predictive value for initiation or progression of coronary artery disease.

Briefly, wave forms will be obtained transcutaneously over the radial or common carotid artery and the right femoral artery, and the time delay is measured between the feet of the 2 wave forms.

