### Statistical analyses

All data will be expressed as means ± SD. Differences between the data of patients for clinical and biological characteristics and basal hemodynamic parameters were analyzed by the nonparametric Mann-Whitney test. Changes in hemodynamic parameters at baseline and the end of follow-up will be analyzed with the paired Student *t *test. Comparisons between coronary artery dimensions at baseline and the end of the study will be made by 2-way ANOVA with repeated measures for experimental condition factor followed by the Fisher protected least-significance difference test.

The Spearman test will be used to find the correlates of coronary endothelium-dependent vasoreactivity. Due to its skewed distribution, urinary albumin excretion rate will be log transformed in the correlation analyses. A backward linear multiple regression will be performed to find the independent predictors for endothelium-dependent coronary vasoreactivity. Statistical significance is assumed when P < 0.05.

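### Arterial stiffness is justified as aortic pulse wave velocity, but the procedure allows a radial or a carotid proximal site, and the radial option measures a different quantity

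*Protocol article*

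**What the plan says.** The Arterial stiffness section of the protocol article first gives its reason for the measure: "The measurement of aortic pulse wave velocity is generally accepted as a very reliable method". It supports this by pointing to simplicity, reproducibility, suitability for repeated comparison and epidemiological evidence of predictive value. A brief account of the procedure follows: "wave forms will be obtained transcutaneously over the radial or common carotid artery and the right femoral artery". What is timed is the interval from the foot of one recorded wave to the foot of the other.

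On timing, "All patients will be evaluated for vascular stiffness at baseline and at the end of follow-up". Table 1 agrees, with arterial stiffness marked at baseline and 60 months only. The stated interest is in change: the section argues that the absence of obstructive disease "empowers in significance prospective changes in arterial mechanical properties".

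The Statistical analyses section does not name arterial stiffness or pulse wave velocity. The nearest provision is for a paired t test: "Changes in hemodynamic parameters at baseline and the end of follow-up will be analyzed with the paired Student".

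**The concern.** The reason given for the measure and the procedure given for it do not match. The reason concerns aortic velocity. The procedure permits two proximal sites, and only the carotid one yields a delay that mainly reflects the aorta.

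Two consequences follow, of different standing.

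- **Pooling.** If some patients are measured radial-femoral and others carotid-femoral, any summary or comparison across patients mixes two quantities. This needs only that both permitted options are used.
- **Change over 5 years.** If a patient's site differs between the two visits, the recorded change contains the difference between paths as well as any arterial stiffening. This is conditional on a switch.

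The evidence and reliability that the section cites for aortic velocity also do not carry over to radial-femoral values, even where the radial site is used consistently.

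**Working it through.** The article states no velocity, standard deviation, effect size or power figure for this measure, so there is no figure to reproduce. The check is first a comparison of definitions, then an illustration on assumed values.

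**1. The two permitted quantities**

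Let T_c, T_r and T_f be the times the pulse takes from the heart to the carotid, radial and femoral sites. The article times the delay between the feet of the two wave forms, so:

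- carotid-femoral delay = T_f − T_c
- radial-femoral delay = T_f − T_r
- difference between them = T_r − T_c

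The carotid site is near the heart, so T_f − T_c is mainly aortic travel. T_r includes the length of the arm. The difference T_r − T_c is arm travel against neck travel and does not involve the path to the groin. If the arm arteries stiffen, T_r falls and the radial-femoral delay rises with no change in the aorta. This is anatomy and algebra; the article does not state it.

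**2. What the article fixes**

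The Patients section requires the same projections, field and catheter sizes at repeat angiography and treats this as essential to the 5-year comparison. The Arterial stiffness section names two alternative sites and does not say when each applies.

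**3. Illustration in m/s**

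Assumed, not in the documents: path difference d = 1 to 2 m/s; share of patients with a different site at the two visits q = 0.10 to 0.30, or zero if every patient keeps one site; SD of change without switching = 1.5 m/s.

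- No switching: bias = 0.
- All switches in one direction: bias = q × d, from 0.10 × 1 = 0.1 to 0.30 × 2 = 0.6 m/s.
- Switches equally likely in either direction: SD = √(1.5² + q × d²). This runs from √(2.25 + 0.10) = 1.53 to √(2.25 + 1.20) = 1.86 m/s. The variance ratios are 2.35/2.25 = 1.04 and 3.45/2.25 = 1.53, so 4% to 53% more variance.

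**4. Illustration as a false-positive rate**

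Inputs from the article: 600 patients ("The study will enroll 600 patients with type 2 diabetes") and the 0.05 level ("Statistical significance is assumed when P < 0.05"). Assumed: a two-sided paired test, true change zero, a net share f switching in one direction, and a site difference D in units of the SD of within-patient change.

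Spurious mean change = f × D; SD = √(1 + f(1 − f)D²); z = f × D × √n / SD; rejection rate = Φ(z − 1.96) + Φ(−z − 1.96).

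Example with n = 600, D = 0.5, f = 0.10: mean change = 0.05; SD = √(1 + 0.09 × 0.25) = 1.011; z = 0.05 × 24.49 / 1.011 = 1.21; rejection rate = 22.8%.

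| n | D | f = 0 | f = 0.05 | f = 0.10 | f = 0.20 |
|---|---|---|---|---|---|
| 600 | 0.5 | 5.0% | 9.3% | 22.8% | 67.1% |
| 600 | 1.0 | 5.0% | 22.3% | 65.0% | 99.5% |
| 480 (assumed pairs) | 0.5 | 5.0% | 8.5% | 19.2% | 57.5% |
| 480 (assumed pairs) | 1.0 | 5.0% | 18.8% | 55.5% | 98.3% |

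The f = 0 column is what a fixed site delivers. The other columns show only that a modest one-directional drift would matter at this sample size. They do not show that such drift is expected.

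**The case against.** The strongest reply is that this is a journal article and the procedure is openly given in brief. Same-site rules, side and distance conventions are details that a full protocol or device manual usually holds, so their absence here is no fault. The section also calls the method reproducible and suited to repeated comparison, which suggests like-for-like repetition. If each patient keeps one site, the site-switch bias in the paired change is exactly zero.

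Much of that stands.

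- A reader might infer that 5-year changes in this study will be confounded by changes of site. The documents do not support that: nothing says or implies that sites will change.
- A reader might take it as settled that pulse wave velocity is analysed by the paired t test or enters the correlation and regression analyses. The Statistical analyses section names it in none of these. The paired t test for hemodynamic parameters is its most natural place, but that is an inference. The Spearman test and backward regression are described for coronary vasoreactivity.
- The article endorses aortic velocity as a method; that it is the quantity measured is implied rather than stated.
- Every magnitude above rests on assumed inputs, and the upper figures need the extremes of those assumptions together.
- Stiffness is one of many measures. Methods/Design also plans vascular reactivity and endothelial function at both ends of the study.

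The reply does not remove the choice of sites. The article states two alternatives, one of which does not give the quantity used to justify the measure. That is a rule fixed badly, not a detail left out. If a manual fixes one site, this sentence disagrees with it and still needs correcting.

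**Conclusion.** The point holds in a limited form. The radial option does not deliver the aortic velocity on which the section relies, and pooled values can mix two quantities whether or not any patient changes site. Distortion of the 5-year change is a possibility that the text leaves open, not an established flaw. It is zero if each patient keeps one site, and otherwise of unknown size.

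The conclusion rests on the wording of the Arterial stiffness section and on the anatomy of the two paths, not on the illustrative figures. It is a minor-to-moderate issue, confined to a measure not named as primary.

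**What to change.** In the Arterial stiffness section, delete the radial alternative so that the common carotid is the proximal site for all patients at both visits, giving carotid-femoral velocity. Record the site used at each examination.

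Where a radial baseline already exists, repeat the radial site at month 60 and analyse those pairs separately. A radial-radial pair carries no site-switch bias, so it need not be discarded, but it should not be pooled with carotid-femoral values.

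The cost is a small wording change, one recorded item and a separate summary for any radial pairs. The downside is that a few patients with unusable carotid signals, and those with radial baselines, would not contribute to the main aortic velocity summary.
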